## Abstract

**Background:**

Musculoskeletal pain (MP) has today intensified in a large proportion of music students in Iran. Poor posture while playing an instrument is thus assumed as a very significant risk factor affecting such a condition in this population. The present study aims to evaluate the impact of electronic learning (e-learning) for postural education to music students on posture behavior and MP (abbreviated as an El-Poems study).

**Methods:**

This study is a matched-pair, two-arm, parallel randomized controlled trial (RCT). The participants, as the 7th-to-12th-grade music students, will be accordingly assigned to intervention (*n* = 204) and control (*n* = 204) groups, based on the inclusion and exclusion criteria. The postural education will be also presented through the web-based Student Education Network (with the acronym, SHAD) at the Tehran Conservatory of Music, Tehran, Iran. The intervention program consists of four sessions, using the Integrated Change (I-Change) model. It will be also implemented by a trained physical education instructor and a health educator. The content of the program includes raising awareness, building motivation, and developing skills. Besides, its components are comprised of specific proper postures viz. standing, sitting, lifting, carrying, and hand position while playing a musical instrument. The primary outcome is the MP that will be assessed by the Nordic Body Map (NBM) questionnaire and a numerical rating scale (NRS), and the secondary outcome is the posture behavior that will be evaluated objectively, using the Rapid Entire Body Assessment (REBA) tool. The data will be also collected at baseline and after a six-month follow-up.

**Conclusion:**

This RCT is an innovative study as a pioneer to represent the first attempt for web-based postural education as well as an attractive intervention to prevent MP in Iranian music students.

**Trial registration:**

Current Controlled Trials IRCT20180528039885N2. Prospectively registered on 11 September 2021

## Background

Due to their unique jobs and conditions, music students are at higher risk of playing-related musculoskeletal pain (PRMP), as compared with their peers involved in other disciplines [1–3]. Musculoskeletal pain (MP) in this population is often diagnosed as chronic, and it often occurs because of repetitive movements, poor posture, or carrying heavy musical instruments [1]. However, acute pain is seen due to a sudden increase in instrument practice time [4]. Studies have so far reported the lifetime prevalence of MP in music students by 41–93%, wherein the upper limbs and the spine have been mostly affected [4–8]. In this line, Mehrparvar et al. (2012) had observed that 44.4% of Iranian musicians were suffering from MP [9].

Of note, MP leads to lower quality of life and even significant disabilities in music students, as a serious threat to their performance quality [5, 9–11]. Ultimately, these problems cause depression and anxiety and consequently impose heavy costs on communities. Sometimes, musicians are forced to leave their jobs to recover, but there is an increased likelihood of subsequent injuries, temporary or permanent [12]. Therefore, such problems reveal that a specific postural education program for music students, to guide them how to prevent MP, can significantly improve their performance and quality of life.

Music students at this age are able to assume personal responsibilities for changing their behaviors and choices [13]. Unfortunately, MP prevention behaviors are less common among music students [14, 15], and there is a rising demand for educating them to take care of their own health and adopt proper postures during music practices [14]. According to Salonen (2018), there is a need to develop more prevention programs to promote health and well-being in music students [16]. Receiving education about proper postures and promoting postural behaviors during music practices also play key roles in MP prevention during adulthood and career life [13, 14].

Unfortunately, few studies have thus far implemented and evaluated MP prevention programs among music students [17]. For example, in a recent randomized controlled pilot study by Wolff et al. (2021), the impact of an MP prevention workshop among 57 music students had been assessed. At the 8-week follow-up, the intervention group had accordingly demonstrated a 32% reduction in their pain score, but the controls had shown an 8% increase in pain (*p* < 0.01) [18]. In Davies (2020), the effects of the Alexander Technique classes for music students on MP had been further investigated, and pain reduction had been particularly reported [7]. Cyga´nska et al. (2020) had similarly explored the impact of chair massage and exercise on MP in music students and found an upward trend in pain threshold in both intervention groups compared with the controls [19]. Other studies have also suggested various interventions to relieve MP in music students, using a randomized controlled trial (RCT) [14] and comprehensive health programs during the school year [20]. The educational content in these studies has often covered information about the structure of the musculoskeletal system and the importance of proper posture while playing a musical instrument, wherein the positive effect of such interventions on MP have been confirmed [14, 20]. However, no research has so far developed and implemented an MP prevention program among music students in Iran, to the best of the authors’ knowledge.

In the study by Stanhope (2018), most participants believed that poor posture was a very important risk factor for MP. They generally agreed with the practical workshops about injury prevention strategies, and only 14% of them preferred interactive web-based learning [21]. Before the coronavirus disease 2019 (COVID-19) pandemic [22], education at music conservatories was simply dependent on face-to-face learning, but this disease was a serious threat to this type of learning according to the declaration released by the World Health Organization (WHO) [22].

Although face-to-face learning is a real-time communication between educators and learners, and even provides immediate feedback, it is influenced by place, time, and close contacts [23]. Also, it is alleged that instruction through electronic learning (e-learning) occurs at different times and/or places, from any distance, via various forms of training materials [24–26]. Therefore, the role of e-learning is valuable, particularly for today’s adolescents as digital natives living under pandemic conditions [27].

In this regard, Park et al. (2011) had examined the effect of a web-based program on back health knowledge and self-efficacy among elementary school children [28] and revealed that posture knowledge and self-efficacy had significantly promoted in the intervention groups compared with the controls, but the changes in posture behavior were not significantly different. Also, Ingle et al. (2014) had evaluated the effectiveness of a web-based health promotion course on Playing-Related Musculoskeletal Disorders (PRMDs) in tertiary music students [29], and highlighted the need for postural education to prevent performance-related musculoskeletal injuries. They also believed that this type of research was likely to be applicable to student musicians.

Nowadays, web-based learning or e-learning is extensively used by most students. As a result, it is an effective method to gain access to more audience easily and securely, facilitate wide information sharing, and influence attitudes, beliefs, and health behaviors [30]. Accordingly, this trial aims to evaluate the impact of e-learning for postural education to music students on the prevention and reduction of MP and posture behavior in this group (abbreviated as an El-Poems study).

Among the behavior change models, the Integrated Change (I-Change) one has been so far utilized to explain a variety of health behaviors. It assumes that at least three main phases can be distinguished in the behavioral change process, viz. awareness, motivation, and skills development [15]. Accordingly, raising awareness of MP in music students is the result of their accurate knowledge and risk perceptions about their own posture behaviors. Building motivation to promote posture behavior also depends on music students’ attitudes (i.e., the outcomes of perceived advantages and disadvantages of posture behavior), social influence (namely, norms, posture behavior, and support of others), and self-efficacy expectations (viz. perceived ability to perform posture behavior). Additionally, developing the essential skills for this purpose is required for posture behavior. The three key factors of the I-Change model are thus incorporated into the El-Poems study to provide a scientific explanation for designing health promotion interventions among music students [15].

### Hypotheses

The primary hypothesis is that MP rate and intensity in the intervention group will reduce, compared with the controls. Also, the secondary hypothesis is that the intervention group will modify their posture behavior, compared with the control group.

## Methods

### Trial design

This study is a matched-pair, two-arm, parallel randomized superiority-controlled trial (RCT), which will be conducted at the Tehran Conservatory of Music, Tehran, Iran, in the 2021–2022 school year. The educational intervention is presented through the web-based Student Education Network (with the acronym, SHAD), initiated by the Ministry of Education to pave the way for sustaining the process of education and learning in the country amid the COVID-19 outbreak.

### Participants

The study participants are music students of Tehran Conservatory of Music, Tehran, Iran, in 7th to 12th grades. They will be eligible to enroll in the study if they agree with the conservatory principals and their parents sign a written consent form for their participation. Also, informed consent of voluntary participation in the study, ability to attend the educational sessions, and e-learning experience are among the inclusion criteria. The participants are also excluded from the study if they have previously received postural education, show reluctance for participation, and have a history of underlying diseases, injuries, or disorders or an unhealthy musculoskeletal system.

### The El-Poems intervention

THE intervention program consists of four sessions, each one lasting for 90 min with a 1-week interval. The program will be accordingly implemented by a trained physical education instructor and a health educator. The educational content of the given program is developed with reference to previous studies [11, 12, 14, 15, 18–23]. The music students in the control group also receive a little information about the hearing health. In addition, there are no concomitant interventions that are prohibited during the trial.

The educational program includes three components of raising awareness, building motivation, and developing skills (Table 1), as explained below:*Raising awareness*: It is comprised of a theoretical session to raise awareness and promote knowledge about the importance of proper posture during the playing along with brief explanations about the anatomy and physiology of the musculoskeletal system as well as the basic body posture in relation to playing a musical instrument, warming-up and cooling-down, stretching, relaxation, instrument-specific biomechanics, and ergonomics.*Building motivation*: This component involves one session, including creating positive attitudes toward paying attention to ergonomic postures during playing and benefits of proper posture behavior, social influence (viz. norms, behavior, and support of others), and self-efficacy expectations (namely, perceived ability to perform posture behaviors).*Developing skills*: It consists of two practical sessions, containing attention to body posture during playing a musical instrument, proper posture while standing, sitting, lifting, and carrying instruments, upper limb position, special stretching exercises, and warming-up before playing.

**Table 1 Tab1:** Content, timeline, components, methods, and responsibilities of the El-Poems study

Content	Components	Methods	Who
Session 1. Promoting in awareness Date: 1–4 December 2021	Improvement of knowledge about importance of proper posture during playing; a brief review of the musculoskeletal system’s anatomy and physiology; to explain about: basic body posture in relation to playing a musical instrument (e.g., standing, sitting, upper limbs, lifting, and carrying position), warming-up and cooling-down, stretching, relaxation, instrument-specific biomechanics, and ergonomics	- Lecture	Main investigator, conservatory health educator
		- Brainstorm, Q & A	
		- Showing Power Point, - Uploading posters, pamphlets, text, ...	
Session 2. Promoting in motivation Date: 6–9 December 2021	Creating a positive attitude toward paying attention to proper postures during playing and its advantages; social influence beliefs (norms of others, behavior of others, and support of others); and self-efficacy expectations (the perceived ability to perform posture behavior)	- Group discussion	Main investigator, conservatory health educator
		- Modeling	
		- Increase risk perception	
		- Benefits of proper posture	
		- Recording participants’ thoughts and experiences about proper posture	
Sessions 3 and 4. Development of skills Date: 11–23 December 2021	Improvement of participants’ abilities to accomplish proper posture behavior: implementation of paying attention to body posture during playing a musical instrument, having proper posture while standing, sitting, lifting and carrying musical instrument, upper limbs position, and practicing special stretching exercise and warming up before playing	- Direct experience	Main investigator, Conservatory physical education instructor and health educator
		- Vicarious experience	
		- Demonstration, re- demonstration	
		- Verbal persuasion	
		- Corrective feedback	

During four online sessions in total, all music students in the intervention group are encouraged to participate in the discussions and ask their questions.

### Outcomes and measures

The participants will complete a short demographic characteristics form containing items about age, gender, grade, instrument type, and weekly playing time. The primary outcomes are:The presence of MP, which is assessed using the Nordic Body Map (NBM) questionnaireThe intensity of pain that will be evaluated via a numerical rating scale (NRS) questionnaire, wherein the participants are asked to circle the number between 0 and 10 that fits best to their pain intensity. Also, zero represents “no pain at all” whereas pain ratings between 1 and 3 indicate mild pain, 4 to 6 show moderate pain, and 7 to 10 denote severe pain

To collect these self-reported data, a link to the online questionnaire is posted in two WhatsApp groups supervised by the class teacher. In addition, there are no missing data due to the obligation to answer all questions.

The secondary outcome takes account of posture behavior, estimated through the Rapid Entire Body Assessment (REBA) tool by observing and filming the body positions of the music students during specific postures while playing a musical instrument through the SHAD platform. One independent trained rater blinded to the study will also observe and record the participants’ postures. Each posture is initially given a score. Then, the posture scores are estimated based on the diagram shown in Fig. 1. The final REBA score will be between 1 and 15 and divided into five levels in terms of risks: 1 = negligible risk, 2–3 = low risk, 4–7 = moderate risk, 8–10 = high risk, and 11–15 = very high risk [31].

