### Sample size

Sample size calculation is based on the study by Mehrparvar et al. (2012) on MP among Iranian instrumentalists [9], wherein the prevalence of MP in music students had been reported about 44% (p1 = 0.44). If it is assumed that the given rate will decrease to 30% (p2 = 0.30) after the El-Poems intervention, a trial consisting of 185 music students per group would have 80% power (*β* = 0.2) at the 5% significance level (*α* = 0.05). To assume a 10% dropout for each group, at least 204 samples in each group will be needed for the El-Poems study. The following formula is accordingly applied to calculate the sample size:$$n=\left\{{\left({Z}_{1-\upalpha /2}+{Z}_{1-\upbeta}\right)}^2\times \left[{p}_1\left(1-{p}_1\right)+{p}_2\left(1-{p}_2\right)\right]\right\}/{\left({p}_1-{p}_2\right)}^2$$

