### Randomization

Totally, there are two national music conservatories in Tehran, Iran. Since individual allocation is not possible in a conservatory’s context, the classes at each conservatory are first randomly divided into two matched groups based on the number of students, grade, and gender. Then, the groups are numbered as 1 and 2 and placed in the bowl. A neutral person is next asked to pull out one of the numbers from the bowl. The group number 1 is thus assigned to the intervention group and 2 is given to the controls. The main researcher also supervises the randomization steps. The current RCT protocol is reported in compliance with the Consolidated Standards of Reporting Trials (CONSORT) guidelines. The El-Poems study flowchart is depicted in Fig. 2.

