### Statistical analysis

The data will be analyzed using the SPSS Statistics software package 24.0 (IBM SPSS 24.0 Ink, NY: IBM Corp). All continuous variables will be also assessed for their normal distribution. *T*-test, Mann-Whitney *U* test, and chi-square test will be then utilized to compare the baseline measurements. The descriptive statistics are also reported to investigate the data. To obtain the time period (at baseline and 6-month evaluation, as the test time factor) in which the difference in mean scores within the groups (viz. group factor) originates, the two-way analysis of variance (ANOVA) will be exploited. The test for homogeneity of the data is further employed for the between-participant variables. Since we do not have a variable with more than one pair, confidence interval adjustment is not selected. The Wilcoxon signed-rank test is additionally calculated for the difference in the MP rate between both study groups. Moreover, the effect sizes will be calculated using the partial eta-squared measure (ηp^2^) that gives the idea of how different the participants are. The significance level will be set at *p* < 0.05.

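### Instrument type and weekly playing time are collected and plausibly prognostic, but they are neither matched on nor used in any outcome analysis, which leaves a modest and avoidable amount of noise in the arm comparison

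*Protocol article*

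**What the plan says.** Four places in the protocol article bear on this.

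- **Collected.** Outcomes and measures: "The participants will complete a short demographic characteristics form containing items about age, gender, grade, instrument type, and weekly playing time".
- **Plausibly prognostic.** Background, on musculoskeletal pain (MP) in music students: "it often occurs because of repetitive movements, poor posture, or carrying heavy musical instruments". It adds that "acute pain is seen due to a sudden increase in instrument practice time". REBA is scored from film of the student playing, and the intervention teaches biomechanics specific to each instrument, so it is a fair inference that instrument affects the posture score as well.
- **Not balanced.** Randomization: "the classes at each conservatory are first randomly divided into two matched groups based on the number of students, grade, and gender". Instrument and playing time are not in that list. A draw then decides which group receives the intervention.
- **Not used for outcomes.** Under Statistical analysis, baseline variables are given one role: a t-test, a Mann-Whitney U "test, and chi-square test will be then utilized to compare the baseline measurements". Mean scores go to a two-way ANOVA with group and time as factors, and the MP rate to a Wilcoxon signed-rank test. No covariate is named for either.

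**The concern.** The plan holds two baseline variables that its own Background connects with pain, and it uses them only to compare the arms at baseline. Under random allocation such tests can detect only chance differences, and nothing in the plan follows from their result.

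Whole classes are allocated, so a few classes with many heavy instruments or many practice hours can fall in one arm more easily than if students were allocated one by one. The resulting difference in expected pain or posture score then forms part of the random error of the arm effect. Variation between students that these variables explain also stays in the error term. Modelling class, or adding grade and gender, would not bring either variable into the analysis. Adjusting for the baseline outcome would do so only in part. What is at stake is precision, on MP presence, NRS and REBA alike.

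**Working it through.** **1. The plan's own scale.** Inputs from Sample size: "the prevalence of MP in music students had been reported about 44% (p1 = 0.44"), "the given rate will decrease to 30% (p2 = 0.30) after the El-Poems intervention", and "a trial consisting of 185 music students per group would have 80% power", with two-sided alpha 0.05. The printed formula gives

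n = (1.960 + 0.842)² × [0.44×0.56 + 0.30×0.70] / 0.14² = 7.849 × 0.4564 / 0.0196 = 182.8, so 183.

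The pooled-variance version gives 186, so the stated 185 is reproduced closely. For 10% dropout, 183/0.9 and 185×1.1 both round up to 204, as stated, and 185/0.9 gives 206. The point does not depend on this calculation. It supplies the yardstick: a 14-point target and a planned standard error of √(0.4564/n), which is 4.7 points at 204 per arm and 5.0 at 185.

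**2. Chance imbalance.** The document gives no class size, intraclass correlation or covariate distribution, so these are assumed: 40% of students are high-risk by instrument or load, there are m students per class, the correlation of that status within class is ρ, and any help from matching is ignored.

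SD of the arm difference in share = √{2×0.4×0.6/204 × [1 + (m−1)ρ]}

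- Individual allocation (ρ = 0): √(0.48/204) = 4.9 points
- m = 15, ρ = 0.05: factor 1.7, 6.3 points
- m = 25, ρ = 0.20: factor 5.8, 11.7 points

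**3. What an imbalance does to a follow-up MP difference.** Shift = imbalance × risk gap.

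- 5 points × 10 points: 0.05 × 0.10 = 0.5 points, 4% of 14
- 10 points × 20 points: 0.10 × 0.20 = 2 points, 14% of 14
- 20 points × 30 points: 0.20 × 0.30 = 6 points, 43% of 14

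The last case is extreme. A 20-point imbalance is 20/11.7 = 1.7 SDs under the widest assumption above and 20/6.3 = 3.2 SDs under the narrower class-based one.

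**4. What the two covariates add beyond baseline MP.** This is a simulation of 800 trials per scenario. Assumptions: 24 classes of 17 in 12 pairs (408 students), four instrument families with an MP log-odds spread of ±0.4 to ±0.7, and an odds ratio of 1.3 to 1.5 per SD of weekly hours. The table gives the SD of the arm estimate in points, with smaller then larger assumed effects.

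| Classes | Unadjusted | Baseline MP only | Plus instrument and hours | Variance ratio, last two |
|---|---|---|---|---|
| Mixed | 4.77; 5.09 | 4.42; 4.50 | 4.35; 4.33 | 0.97; 0.93 |
| Partly grouped | 5.21; 5.65 | 4.77; 4.90 | 4.56; 4.35 | 0.92; 0.79 |
| Grouped by instrument | 5.46; 6.75 | 4.86; 5.40 | 4.67; 4.44 | 0.92; 0.68 |

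The ratios agree with the squared SDs up to rounding, for example 4.35²/4.42² = 0.97 and 4.44²/5.40² = 0.68.

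Baseline MP alone does more with mixed classes: 4.42²/4.77² = 0.86 and 4.50²/5.09² = 0.78, a reduction of 14-22%. The further step is 3-7%. With 800 trials the relative error of each SD is about 1/√1600 = 2.5%, so the 3% is an order of magnitude.

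**5. In power terms, mixed classes.** Power = Φ(14/SD − 1.96). From SD 4.42 to 4.35 it moves from about 89% to 90%. From 4.50 to 4.33 it moves from about 88% to 90%. The gain is one to two points.

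**6. A continuous outcome such as NRS.** If the two variables explain 2%, 5%, 10% or 20% of the variance otherwise left in the error, then 185 × (1 − R²) gives the same 80% power with 182, 176, 167 or 148 per arm. At 185 per arm, power would be about 81%, 82%, 84% or 88%.

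**The case against.** The strongest reply is that this is a journal article. Lists of covariates belong in an analysis plan, and an unadjusted randomised comparison is valid. That stands: the plan makes no error here and contradicts nothing. But the article does not leave the analysis open. It fixes the matching factors and names its tests, and one of them, the Wilcoxon signed-rank test, cannot take a covariate. Improving a stated choice is fair comment.

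Four stronger readings are tempting, and the document does not support them.

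- **That the arm effect is biased.** Classes are divided at random, so imbalance is sampling error, which an analysis that accounts for class reflects in its standard error.
- **That imbalance passes straight into every outcome.** If the ANOVA effect is read as group-by-time, a stable additive effect of instrument largely cancels between baseline and 6 months. REBA is probably well protected, since most students would play the same instrument at both visits. Effects on change do not cancel, and an MP comparison at follow-up only has no such protection.
- **That the gain could be about a third.** The 32% comes from one scenario of six, with classes formed by instrument and the largest assumed effects. The article describes classes only by size, grade and gender. With mixed classes, the unadjusted SDs of 4.77 and 5.09 are close to the planned 4.7 and 5.0, so that noise is already in the sample size.
- **That the Background names habitual playing hours as a cause.** It speaks of a sudden increase in practice time. Baseline weekly hours are a plausible but indirect measure of that.

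**Conclusion.** The point holds as a low-priority suggestion on precision. Both variables are collected, plausibly prognostic, unmatched and absent from the named outcome analyses, so part of the chance noise in the arm comparison is avoidable. With mixed classes, adjusting for them beyond baseline MP would lower the variance by about 3-7%. Only if classes are grouped by instrument would it be more (8-32% in the simulation), and nothing in the document says that they are. These sizes rest on assumed class numbers, instrument effects and hours effects. The document gives none of these, so it cannot place the trial within the range. The validity of the comparison is not in question on this ground.

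**What to change.** Amend Statistical analysis to pre-specify instrument family (a few groups, for instance four, fixed before the 6-month data are seen) and baseline weekly playing time (linear) as covariates. They should stand alongside the baseline value of the outcome, in 6-month models for MP presence, NRS and REBA that account for class. Report the adjusted risk difference for MP and adjusted mean differences for NRS and REBA. Show the two variables by arm in a descriptive table in place of significance tests.

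The cost is wording, about four degrees of freedom (three for four families, one for hours), and the need to settle the instrument grouping in advance. No new data, visits or participants are needed. Settling this before follow-up data are seen also avoids any suspicion that the covariates were chosen for their effect on the result.

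### The filmed REBA assessment cannot separate trained performance on camera from habitual playing posture, so an arm difference should not be read as changed habit

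*Protocol article*

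**What the plan says.** The secondary hypothesis (Hypotheses) is that the intervention group will change its posture behaviour relative to controls. The abstract's Methods paragraph states that "the secondary outcome is the posture behavior that will be evaluated objectively", and the Discussion counts the observational tool among the trial's advantages.

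Outcomes and measures describes the measurement as "observing and filming the body positions of the music students during specific postures while playing a musical instrument through the SHAD platform". One independent, trained, blinded rater observes and records the postures. Data are collected one week before the programme and six months after it.

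The intervention is also delivered through SHAD (Trial design). The abstract says that it covers "specific proper postures viz. standing, sitting, lifting, carrying, and hand position while playing a musical instrument". Table 1 lists "Demonstration, re- demonstration" and "Corrective feedback" among the methods of sessions 3 and 4. For the other arm, the section on the intervention says: "The music students in the control group also receive a little information about the hearing health". It describes no posture practice for controls.

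**The concern.** The hypothesis is about behaviour, which most readers will take to mean how students usually hold themselves when they play. The measurement is a film made on the platform where one arm, and only that arm, was shown good playing posture, performed it and was corrected. At follow-up the intervention students have been taught what a well-scored posture looks like, and the controls have not. Some intervention students may show that posture for the length of the recording and play as before at other times.

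What is at stake is the meaning of a positive secondary result. A lower REBA score in the intervention arm could be reported as an objectively measured change in behaviour when part or all of it is skill shown under observation.

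**Working it through.** The point concerns what the outcome measures, so the main check sets the relevant statements side by side.

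**1. Training and test settings**

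| Feature | Intervention sessions | REBA assessment |
|---|---|---|
| Platform | SHAD (Trial design) | SHAD (Outcomes and measures) |
| Content | Named proper postures, including hand position while playing (Abstract, Methods) | Particular postures while playing, not listed (Outcomes and measures) |
| What students do | Perform the posture and are corrected (Table 1, sessions 3 and 4) | Are observed and filmed |
| Who takes part | Intervention arm only | Both arms |

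The test closely resembles the training, and the resemblance exists for one arm only.

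**2. Do the stated safeguards remove the difference?**

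- *Blinded rater.* This prevents allocation from influencing the score. It cannot affect what the student does while being filmed.
- *Same filming in both arms.* A camera response common to both arms would cancel in the comparison. A response that depends on having been taught what to show would not.
- *Baseline film.* It is made before the sessions, so adjusting for it cannot remove a response that the sessions create.
- *Six-month interval.* This may weaken recall of the lesson. Nothing in the assessment separates recalled technique from habit.

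**3. Is there any step aimed at habitual posture?** The article describes no sampling of ordinary practice and no filming designed to leave posture unprompted. It also does not say that students are told to adopt a posture.

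**4. What arithmetic can add.** The plan's only power calculation is for pain prevalence. Its stated formula with 0.44, 0.30, two-sided alpha 0.05 and 80% power gives n = 182.8, so 183 per group, against the stated 185. With 10% dropout, 183/0.90 gives 204, the stated figure. This is consistent and has no bearing on REBA.

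The document gives no REBA standard deviation (SD) and no size for an on-camera effect. For illustration only, assume an SD of 2 (range 1.5 to 2.5), 184 analysed per arm (204 × 0.90 = 183.6) and no clustering:

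- SE of the arm difference = SD × √(2/184) = 0.21 (0.16 to 0.26).
- Assumed on-camera gain of 0.5 point: z = 0.5/SE = 2.40 (3.20 at SD 1.5, 1.92 at SD 2.5). The chance of p < 0.05 is 67% (89% and 48%).
- Assumed gain of 1 point: z is at least 3.84, so the chance is at least 97%.

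These figures show only that a trial of this size could detect a shift of the assumed size. They do not show that such a shift occurs. Classes are allocated as groups (Randomization), and positive clustering would enlarge the SE and lower these percentages.

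**The case against.** The strongest reply is that students are filmed while actually playing, six months after the programme, and nothing says that they are prompted, shown a model or reminded of the lesson. A retained change in habit fits the text equally well. This stands, and it rules out several stronger readings that a reader might infer:

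- *That REBA shows reproduction of the lesson rather than habit.* The documents do not support this. Both may contribute, and the defect is that they cannot be separated.
- *That the filmed postures are the taught ones.* The overlap is inferred from similar wording. The filmed postures are not listed, and the taught set covers "attention to body posture during playing a musical instrument, proper posture while standing, sitting, lifting, and carrying instruments". Lifting and carrying are not playing postures, so the two sets cannot be identical as described.
- *That controls cannot improve on camera.* They are filmed too and may adjust. Only a difference between arms in what they know to show is supported.
- *That the illustrative percentages measure the bias.* They rest on an assumed shift and an assumed SD.
- *That a pain effect would be formally attributed to posture.* The Statistical analysis section plans no mediation analysis.

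It can also be said that filming instructions and scoring times belong in a fuller protocol or rater manual. That is fair as to detail, and their absence from an article is not the complaint. The article does fix the main choice: films in particular postures on the training platform, presented as an objective measure of behaviour. No later analysis can recover habitual posture from such films if they capture performance.

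Finally, reactivity to observation affects any openly observed behaviour. That is true, but here training and test share a setting in one arm only, and a modest change would reduce the problem.

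**Conclusion.** The concern holds in limited form. As described, the REBA assessment cannot separate trained performance on camera from habitual playing posture, and neither rater blinding nor the baseline film removes this. A between-arm difference would support a statement about posture under filmed observation, but would not by itself establish changed habit.

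The size of any such effect cannot be estimated from the document. The conclusion rests on three documented facts: the shared platform, filming in particular postures, and posture practice with correction in one arm only. It also rests on one inference, that the filmed and taught postures overlap at least for playing positions. It does not assume that students are prompted. The issue is confined to the secondary outcome; the primary pain outcomes are not measured this way.

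**What to change.** In Outcomes and measures, specify that every student in both arms, at baseline and at six months, is filmed playing the same kind of ordinary, uninterrupted passage under a neutral instruction that does not mention posture. State that the existing blinded rater scores pre-set time points after the opening minute.

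The cost is a changed filming instruction and slightly longer clips, with no extra staff. It reduces the problem without removing it, because some students will still guess the purpose.

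If set postures are kept, describe the outcome as posture under filmed observation, or posture skill. Limit the secondary hypothesis and conclusion to that, and qualify the abstract's claim of objective evaluation accordingly. This costs only wording.

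Mixing films from both arms and both time points in random order is an optional addition. It protects the scoring, not the performance.
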